### Intervention Procedures

Before the start of the trial, research team members received training by the principal investigator on how to collect data by tablet, conduct recruitment, implement group allocation, conduct follow-up phone calls, and monitor times to call participants. The schedule of enrollment, interventions, and assessments is shown in Table 2.

**Table 2 table2:** Protocol schedule of enrollment, intervention, and assessments for M528 (average length of study duration is 36-38 weeks).

		Women at 28-34 weeks gestation	1 day after enrollment	At 36 weeks	Delivery	Age of child in months					
**Enrollment**						1	2	3	4	5	6
	Eligibility assessment, consent, assignment, and allocation	x									
**Interventions**											
	Both groups receive texts		x	x	x	x	x	x	x	x	x
**Assessments**											
	Baseline survey	x									
	Delivery check by text and phone calls			x	x						
	Follow-up phone calls to assess										
	Postdelivery status					x					
	Feeding follow-up status					x	x	x	x	x	x
	Child morbidity and self-efficacy scale					x		x		x	
	Social desirability scale										x
	Evaluation on mHealth (intervention group): phone-based survey and qualitative study										x

### Intervention Group

Implementation was organized in 2 phases, preparation and intervention service delivery.

#### Stage 1: Preparation Phase

In developing text messages, we reviewed infant feeding literature including United Nations Children’s Fund (UNICEF) and WHO breastfeeding guidelines [6,46]; Australian Ministry of Health breast and infant feeding guidelines [47,48]; Uganda breastfeeding counseling messages [49]; information and communication materials focused on infant feeding educational messages from the Department of Health [50] and Save the Children, Myanmar [51]; a similar study conducted in China [31,37], and findings from our formative qualitative study [16]. This phase was conducted in 2014 to inform the study design and involved in-depth and key informant interviews and focus group discussions with pregnant women and accompanying family members; nurses and doctors from the Central Women’s Hospital; senior managers from the National Nutrition Centre, Department of Health, UNICEF, and international and national nongovernment organizations; and a private mobile company [16]. This provided valuable information for modifying the study instruments—for example, by making the module on service delivery more realistic. One key finding was a need to train mothers, particularly working mothers, on how to manually express breastmilk. We, therefore, adopted the Marmet technique [52] in messages sent at 6 to 12 weeks postdelivery.

Health Belief Models and example text messages.Benefits to child (perceived benefits):Breastmilk contains water and nutrients needed for your baby and is sufficient for the first six months of life.Breastmilk is best for your child’s memory, brain development, and physical growth.Breastmilk is readily available, convenient, clean, safe, free, and does not need any preparation.Breastmilk will prevent your child from having diarrhea or pneumonia and help them recover quickly if ill.People who were breastfed as babies are less likely to be overweight or obese or have type 2 diabetes than those who were not breastfed.Colostrum (Noh-Oo-Ye), the first yellowish milk, is clean and not dirty. It contains antibodies and prevents your child from getting sick. Do not throw it away.Colostrum (Noh-Oo-Ye) will protect your baby from allergies, infection, and yellow skin and eyes (A-Thar-Wah).Benefits to mothers (perceived benefits):If you breastfeed, your chances of having breast and ovarian cancer later in life will be reduced.Breastfeeding may have a natural contraceptive effect.Breastfeeding will help you reduce your weight after delivery and return to your original shapePerceived barriers—grandmother’s (child’s grandmother) influences in adding water, honey and formula milk:Please share this message with your grandmother: Breastmilk alone has everything your baby needs. It has all the nutrients and water required.Please share this message with your grandmother: Don't use a bottle or teat. Your baby can drink up from a cup—even newborns. Cups should be wide mounted.Don’t give in to peer pressure (from grandmothers and others) when they tell you to use formula milk after delivery.Skilled training approach to overcome the perceived barriers for inadequate milk flow and breast problems:It is important to bring your baby to your breast instead of leaning over to your baby. A good latch and position is important for good milk flow.Make sure you have correct posture and your baby is attached properly. If your baby can suck well, you will have better milk flow and prevent sore and cracked nipples.If you have sore or cracked nipples, breast engorgement, or mastitis, don't give up. Take your baby off your breast for a while and try again in a little while. Also try gently massaging your breast. Frequent breast feeding can reduce pain and produce more breastmilk. If pain persists, tell your midwife or health care practitioner.Skilled training approach to overcome the perceived barriers (especially for women who have to return to work):Plan to breastfeed before you return to work. Arrange with your employers/supervisors (if possible). If you go back to work, your grandmother or another carer may be able to bring your baby to work for breastfeeding.Expressing milk by hand is using your hand to rhythmically compress your breast so that milk comes out. You need to compress the area under the areola (the pink or brown part of the breast) behind the nipple, not the nipple itself.Please keep breastfeeding. Express breastmilk before you go to work. The best time is before and after work and at night time.Expressed milk can be safely stored in the refrigerator for 72 hours and at room temperature for 24 hours. Make sure you put breastmilk in a clean, sealed container.Perceived threat (perceived susceptibility and severity):Do not give water, honey, sweet fluids, or anything else (such as rice powder or porridge) to your baby. These could make your child sick and slow your milk flow.Formula milk may cause your baby to become constipated because it is harder to digest than breastmilk.Formula milk may cause diarrhea if prepared in an unhygienic way.Your breastmilk has all the essential things needed for your baby’s brain and eye growth, whereas formula milk does not.Don’t start giving any semisolid or solid food to your baby before he or she is 6 months old. Your baby’s stomach is too small to digest food yet. It can also cause diarrhea.Self-efficacy (coping efficacy to overcome barriers and to continue EBF):Breastmilk has all nutrients in perfect balance for your baby and is an ideal food for newborns and infants. Do not be pressured by your husband, parents, or in-laws to stop breastfeeding.Don't stop breastfeeding. You can overcome barriers!Congratulations! You have successfully breastfed your child for 6 months. Please continue. Your child will thank you. (Note: Improved self-efficacy is linked with training mothers to EBF.)

We also saw the need to revise the inclusion criteria to include only women past 28 weeks’ gestation because the majority of women who visited the antenatal clinic did so only after they were past this point in their pregnancy. We also revised the required educational status to ability to read and write instead of primary school passed. We sought advice from [name], a certified breastfeeding counselor from the University of Sydney who has had experience working in Myanmar, and antenatal clinic nurses from the study hospital. Developed messages were pretested with 15 pregnant women meeting the inclusion criteria and were revised before finalization. Messages were customized to pregnancy gestation and children’s age and categorized into 2 key periods: 28 weeks of pregnancy to delivery and delivery to the child at 6 months of age. We created messages that were simple, locally acceptable, and culturally appropriate. The developed messages were relevant to early child development milestones and the specific needs of expectant and new mothers in relation to EBF. The focus of the messages in relation to the Health Belief Model (described in the study design section) [33] is summarized in Textbox 2. We set up “delivery check messages” sent out automatically when participants reached 36 weeks’ gestation. An example message sent was “Have you delivered? If yes, please reply 1, if no, please reply 2.” If the server received a reply of 1, then messages were immediately changed from prenatal to postnatal. If there was no response after 38 weeks’ gestation, we followed up with a phone call or checked hospital registrations to ascertain if the participant had delivered.

#### Stage 2: Intervention Service Delivery

The intervention was delivered over 9 months—from recruitment to 6 months postdelivery. Text messages were sent to the intervention group 3 times per week (Tuesday, Thursday, and Saturday) in the evening using CommConnect [35], Telerivet [53], and a local company that has an official contract with mobile operators and experience sending bulk SMS messages. Each text message has approximately 160 characters written in Myanmar fonts (Zawgyi font; Myanmar font systems are not yet standardized but we selected the Zawgyi font because it is the most commonly used font in Myanmar). If a participant withdrew or experienced the death of their child, we stopped messaging. The numbers of messages received were the total number of weeks in the study × the number of messages sent per week. The total number of weeks was 38, assuming that the participant was recruited at 28 weeks’ gestation, delivered at 40 weeks (term pregnancy), and remained in the study until the child reached 6 months. Therefore, the intervention group received up to 114 text messages. All participants received the usual hospital antenatal, intra- and postpartum care, and infant feeding support regardless of their assigned group. See Figure 3 for example text message.

**Figure 3 figure3:**
[figure not shown]
Example of breastfeeding promotion text message.

### Control Group

In designing the control group, we followed the recommendations made in a review article on the design of control groups [54]. To minimize intervention bias, we sent nonbreastfeeding-related text messages with mainly pregnancy- and childcare-related content but at a lower frequency (once per week). Messages were developed after reviewing the literature about pregnancy and childcare education, including WHO online resources [55,56] and information and communication materials about infant feeding produced by the Department of Health [50] and Save the Children, Myanmar [51]. Messages included the importance of following recommended pregnancy care such as taking iron and folic acid regularly, following a balanced diet, getting regular exercise, making regular health center visits, and identifying danger signs before delivery. Examples of message topics after delivery include following recommended baby immunization schedules, how to practice proper infant care, and how to protect the baby from mosquitoes to avoid malaria. Each control participant received an estimated 38 messages (1 per week) over 9 months, which were informed by findings from the formative study [16].

### Outcome Measures

The primary outcome is the rate of EBF at 1 to 6 months of the infants’ age measured at monthly intervals after delivery. Secondary outcomes are median duration of EBF and rates of early initiation of breastfeeding (within 1 hour after birth); predominant breastfeeding; current breastfeeding; bottle feeding; and early introduction of solid, semisolid, or soft foods at 1 to 6 months of infant’s age (measured at monthly intervals) [38-40]. We used WHO infant and young child feeding definitions for this study, and definitions of these outcomes are described in Multimedia Appendix 1 [38].

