**Methods:**

M528 is a 2-group parallel-arm randomized controlled trial with 9 months follow-up from recruitment until 6 months post-delivery. A total of 353 pregnant women between 28 and 34 weeks’ gestation who had access to a mobile phone and were able to read and write have been recruited from the Central Women’s Hospital, Yangon, and allocated randomly to an intervention or control group in a 1:1 ratio. The intervention group received breastfeeding promotional SMS messages 3 times a week while the control group received maternal and child health care messages (excluding breastfeeding-related messages) once a week. The SMS messages were tailored for the women’s stage of gestation or the child’s age. A formative qualitative study was conducted prior to the trial to inform the study design and text message content. We hypothesize that the exclusive breastfeeding rate in the intervention group will be double that in the control group. The primary outcome is exclusive breastfeeding from birth to 6 months and secondary outcomes are median durations of exclusive breastfeeding and other infant feeding practices. Both primary and secondary outcomes were assessed by monthly phone calls at 1 to 6 months postdelivery in both groups. Participants’ delivery status was tracked through text messages, phone calls, and hospital records, and delivery characteristics were assessed 1 month after delivery. Child morbidity and breastfeeding self-efficacy scores were assessed at 1, 3, and 5 months postdelivery. Social desirability was measured at 5 months, and text messages expressing delivery success and user experience were assessed at the end of the study.

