The objective of this study is to implement a mobile phone–based EBF promotion in pregnant women attending the antenatal clinic at Central Women’s Hospital, Yangon, and to evaluate its impact on breastfeeding practices. The primary hypothesis is to test whether breastfeeding promotional text messages can help increase EBF practices in the intervention group. We hypothesize that EBF rates in the intervention group during the 6 months after delivery will be double (30%) that of the control group (15%). Although the Myanmar Multiple Indicator Cluster Survey 2010 reported that 24% of infants younger than 6 months were exclusively breastfed, only 15% of infants were exclusively breastfed until they were 6 months old [4]. We, therefore, set the control group’s EBF rate at 15% and expect that the intervention group will have EBF rate at 30% at the end of the study. This is realistic as other intervention studies using text messages to promote EBF practices have reported a more than 2-fold increase in the odds of EBF. For example, a trial in China found a higher EBF rate at 6 months postdelivery in the intervention group (adjusted odd ratios [AOR] 2.58, 95% CI 1.4-3.7) [31] and a trial in Nigeria showed a similar result (AOR 2.40, 95% CI 1.4-4.0) [32]. Our secondary hypotheses are that receiving breastfeeding promotional text messages will result in higher appropriate infant feeding practices in the intervention group compared to that of the control group. We assessed women’s feeding practices, breastfeeding self-efficacy scales, and delivery and child morbidity characteristics during follow-up. We also conducted a process evaluation at the end of the study. Our findings will also help to provide recommendations on how mHealth-based breastfeeding promotion programs can be further improved for use in wider populations.

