### Sample Size Determination

Stata version 13.0 (StataCorp LLC) was used for sample size estimation and data analysis. Sample size was calculated with the assumptions of 80% power, 5% 2-sided alpha, and 13% expected loss at follow-up. The EBF rate of Myanmar children at 6 months of age was 15% [4], and we hypothesize that EBF in the intervention group will be increased 2-fold. The estimated sample size was 312 (156 per group) and the final sample size requirement was 353 participants to allow for 13% loss at follow-up.

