### Baseline Data Collection

Baseline questionnaires comprised instruments which have been validated and tested for reliability and were adapted from the 2011 Myanmar Multiple Indicator Cluster Survey [4] 2015, Myanmar census questionnaires [36], the 2011 Demographic and Health Survey, Bangladesh [7], and a 2012 study from Shanghai, China [37]. At baseline, participants were asked to provide information on their socioeconomic status, previous pregnancies and breastfeeding history, knowledge and sources of breastfeeding information, confidence to breastfeed and perceived self-efficacy to breastfeed, intention to breastfeed, and intended breastfeeding patterns.

**Table 1 table1:** Summary of instruments used at various times in the M528 trial.

Instruments	Baseline	Postpartum month					
		1	2	3	4	5	6
Individual socioeconomic factors (participant and husband): age, sex, ethnicity, religion, education, occupation	x						
Household factors: income level, wealth index	x						
Previous pregnancy, childbirth and breastfeeding experience	x						
Breastfeeding knowledge level (high/medium/low)	x						
Intention and confidence to exclusively breastfeed	x						
Breastfeeding self-efficacy scores (high/low)	x	x		x		x	
Postdelivery survey: date of birth; place of birth; type of delivery; and child’s birth, weight, and sex		x					
Child morbidity characteristics: signs and symptoms of fever, cough, respiratory tract infection, diarrhea, dysentery		x		x		x	
Breastfeeding and other feeding follow-up module—24-hour recall and 1-month recall		x	x	x	x	x	x
Social desirability scale (high/medium/low)						x	
Process evaluation on mHealth (intervention group only): frequency of text messages received, user-friendliness of the messages received, perceived relevance of messages, trust in messages, understanding of messages, and new information learned or not							x

We will examine the relationship between breastfeeding duration and self-efficacy using self-report Likert scales (no confidence= 1, somewhat confident= 2, sometimes confident= 3, confident= 4, very confident= 5) [38,39]. With 5 levels of responses to 33 items, total scores range from 33 to 165 and will be categorized as low self-efficacy (1 to 82) and high self-efficacy (83 to 165).

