### Data Analysis

Quantitative data were collected via tablets and automatically submitted to the Dimagi server from which we could monitor data and generate reports. Stata software version 13 (StataCorp LLC) was used for data analyses. The intervention and control group outcomes will be compared using intention-to-treat principles [61]. Descriptive analyses were used to summarize participant baseline characteristics and breastfeeding practices. Likert scales were analyzed using Mann-Whitney U tests or cumulative odds ratios and proportions between groups using chi-square tests. Duration of EBF was compared by survival analyses with log-rank tests for between-group comparisons. If differences in baseline characteristics of the groups are identified, multivariable analyses will be undertaken. We report results using the CONSORT guidelines for reporting of randomized trials [62]. As follow-up data collection had to rely on the mothers’ self-reporting alone, we adjusted the potential social desirability bias [43] in our analyses to confirm the accuracy of self-reported outcome measures.

For process evaluation, we used Stata software for survey data analysis. We conducted descriptive analyses to summarize participant baseline characteristics and their experiences and feedback about receiving text messages. Text message delivery success was measured by the frequencies of messages received, and proportions were compared with chi-square tests. For the qualitative study, we used thematic analysis. All digitally recorded interviews were transcribed verbatim in Burmese in Microsoft Word and were reviewed to check for accuracy and translated to English. A list of thematic codes was developed by MPH, which was independently reviewed and verified by AA. The data were then be manually coded by MPH for emerging themes, which were again verified by other investigators and the most relevant themes are summarized in a document.

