## Appendix

Multimedia Appendix 1 Presentation of the study at World Conference in Public Health, Melbourne.

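### The primary outcome is stated inconsistently: one cumulative outcome to 6 months, monthly rates with no deciding age, and a sample size built on a single 6-month comparison

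*Protocol article*

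**What the plan says.** The protocol article describes the primary outcome in several places.

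- Abstract, Methods: "The primary outcome is exclusive breastfeeding from birth to 6 months". This is one yes/no result per infant, covering the whole period.
- Outcome Measures: "The primary outcome is the rate of EBF at 1 to 6 months", assessed each month. This is a set of six rates with no age singled out.
- Introduction: the 15% control rate is described as the share of infants still exclusively breastfed up to six months, and the authors "expect that the intervention group will have EBF rate at 30% at the end of the study". The hypothesis sentence just before speaks of rates over the six months after delivery.
- Sample Size Determination: "The EBF rate of Myanmar children at 6 months of age was 15" per cent, to be doubled, with 80% power and one two-sided 5% alpha. The result is 156 per group, 312 in all, and 353 after an allowance for 13% loss.

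Table 1 lists the monthly feeding module as "24-hour recall and 1-month recall". Follow-Up Data Collection explains that the longer recall runs back to the last contact, or to birth at the first call. Neither recall is named as the one that defines the primary outcome. Data Analysis compares "proportions between groups using chi-square tests" and does not link that test to a particular age.

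**The concern.** A cumulative outcome since birth, a set of monthly rates and a single rate at 6 months are different quantities. They can give different answers in the same trial. The article itself shows how much the definition matters: the Introduction takes two figures from one national survey, 24% for infants under 6 months and 15% for those exclusively breastfed for the full period.

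Two things are at stake. First, readers cannot tell which comparison decides whether the intervention worked. The Results section says follow-up is complete and analysis is under way, so a choice made now could be influenced by the data. Second, the sample size provides for one 5% test. A primary outcome made of six monthly rates either needs a rule for combining them or carries a higher false-positive rate.

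**Working it through.** **1. The statements side by side**

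| Place | Form of the outcome | Deciding age |
|---|---|---|
| Abstract, Methods | Cumulative, birth to 6 months | 6 months |
| Introduction | 15% v 30%; basis of the 15% is cumulative | End of study |
| Sample Size Determination | One proportion, 15% doubled | 6 months |
| Outcome Measures | Rate at each of months 1 to 6 | None named |

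The first three can be read as one endpoint. The fourth cannot be merged with them without a further rule.

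**2. The plan's own sample size**

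Inputs from Sample Size Determination: p1 = 0.15, p2 = 0.30, two-sided alpha 0.05 (z = 1.96), power 80% (z = 0.8416). The mean proportion is 0.225.

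n = [1.96·√(2·0.225·0.775) + 0.8416·√(0.15·0.85 + 0.30·0.70)]² / 0.15²
= [1.96·0.5906 + 0.8416·0.5809]² / 0.0225 = 120.5, so 121 per group (134 with continuity correction).

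The stated 156 is not reproduced. It lies close to the unpooled formula at 90% power, which gives 158. The 353 is 312 × 1.13 = 352.6; dividing by 0.87 would give 359. This is a side remark, but it shows how much spare power there is for one test:

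Power at 156 per group = Φ[(0.15·√156 − 1.96·0.5906)/0.5809] = Φ(1.232) = 0.89.

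**3. False-positive rate if any month counted, unadjusted**

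The upper reference, six independent tests, is 1 − 0.95⁶ = 26.5%. The article gives no correlation between months and no month-by-month rates, so the inputs below are assumptions. The first two rows simulate 156 per arm with no true effect and six two-sided 5% comparisons of proportions. The last two rows draw correlated test statistics directly.

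| Model (assumed) | Chance of at least one p < 0.05 |
|---|---|
| Cumulative EBF, month-1 rate 40 / 50 / 70 / 90%, falling to 15% at month 6 | 14.3 / 15.6 / 17.8 / 19.9% |
| Point-in-time EBF, 70% falling to 15%, latent correlation 0.9 down to 0.3 | 20.1 to 26.0% |
| Test statistics equally correlated at 0.9 / 0.7 / 0.5 / 0.3 | 10.8 / 16.4 / 20.7 / 24.1% |
| Test statistics with correlation decaying over time, 0.9 / 0.7 / 0.5 / 0.3 | 13.3 / 19.9 / 23.5 / 25.4% |

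In the cumulative runs each single-month test rejected in 4.4–5.5% of replicates, as it should. Over all models the range is about 11–26%.

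**4. Cost of adjusting over six months**

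Bonferroni level: 0.05/6 = 0.0083, z = 2.638.
Power at 156 per group = Φ[(1.8735 − 2.638·0.5906)/0.5809] = Φ(0.543) = 0.71.
Reaching 80% would take 187 per group (200 with continuity correction) before loss.

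**The case against.** The strongest reply is that the article never says six tests will be run. Outcome Measures says the rate is measured monthly, and the chi-square clause in Data Analysis is general. Nothing states that a significant month counts as success. A repeated-measures test, or naming month 6, would keep 5%, and such a rule may stand in the analysis plan or full protocol, neither of which is shown. This stands. A reader might infer that the design itself carries an inflated error rate. The documents do not support that, and the absence of a multiplicity rule is not the finding.

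A second reply is that the Abstract, Introduction and Sample Size Determination can be read as one cumulative endpoint, leaving Outcome Measures as the outlier. That is fair, and it helps in choosing the remedy. It does not remove the conflict, because the outlier is the section that formally defines the outcome. An analysis plan could settle the choice, but the published statements would still disagree.

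Two further inferences should not be drawn. One is that power may be lost because the cumulative control rate is below 15%. No lower rate appears in the article, and the Introduction presents 15% as the full-period rate. The other is that the definitions are missing because the appendix cited for them is captioned as a conference presentation. Its contents are not shown, so it may hold them.

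**Conclusion.** The inconsistency holds and can be seen in the article's own text: a cumulative outcome, a set of six monthly rates without a deciding age, and a sample size for one comparison at 6 months. The recall period for the primary outcome is also not stated in the article.

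The size of the consequence is conditional. It arises only if any significant month is taken as a positive primary result without adjustment. The false-positive rate would then be roughly 11–26%, or about 14–20% for cumulative EBF under the assumed decline curves. With a six-way Bonferroni split, power for 15% v 30% at 156 per group is about 71%, below the stated 80%. With a single endpoint and a single test, the error rate is 5% and power is about 89%. Confidence is high in the conflict between the statements and only moderate in any particular error rate, which depends on correlations the article does not give.

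**What to change.** Replace the first sentence of Outcome Measures with one primary endpoint and one test, for example:

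> The primary outcome is exclusive breastfeeding from birth to 6 months under the WHO definition adopted for this trial, derived from the recall since last contact at all six calls and compared between groups by one two-sided 5% test. A woman who reported a disqualifying feed at any call is counted as not exclusively breastfeeding, even if later lost to follow-up.

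What counts as disqualifying must follow the adopted WHO definition. The trial's own list of liquids includes oral rehydration solution, vitamin drops and medicines, so a blanket rule of no other liquid or food may not match that definition.

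Make the rates at months 1 to 5 and the 24-hour version secondary. Use the same wording in the Abstract, Introduction, Sample Size Determination and Outcome Measures.

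Check the choice against the prospectively registered or ethics-approved definition. Because follow-up is complete and analysis has begun, state whether any comparison by arm had been seen when the endpoint was fixed, and report the other versions beside it.

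The cost is wording and disclosure, since all the data are already collected. The small downside is that months 1 to 5 lose confirmatory status.
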